#### Cogmed WMT

The original Cogmed WMT consists of 13 verbal and visual STM and WM tasks, which are implemented using a computer program (Cogmed, Stockholm, Sweden). A child will complete 8 different task on each training session. An example of a verbal WM task is Decoder. In this particular task, some letters will be said aloud, while 3 letters are shown at the same time with the corresponding letter highlighted. The child needs to remember the letters that he/she hears and select the letters by clicking on them without becoming distracted by the other non-corresponding letters shown on the display. An example of a verbal WM task is Rotating data link. In this particular task a number of lamps will be highlighted in a successive order. The child needs to remember the order. Before the child gives an answer, the entire panel will be turned through 90 degrees. When the program says “go”, the child clicks on the circles in the order in which the lamps were highlighted, however they need to remember that the panel has turned 90 degrees. The program is provided on a compact disc and used by the child on a personal computer at home and/or school, supervised by a parent and/or teacher. Responses are made by clicking on displays using the computer mouse. The difficulty level is automatically adjusted, on a trial-by-trial basis, to match the WM span of the child on each task. Children are assigned a unique ID code and task performance is uploaded in a log file. During the training sessions the child receives positive verbal feedback from the computer. In addition to this high scores are displayed after each task; there is also an “energy” counter which can be used on a fun racing game completed after each training day. The racing game is only included as a reward and does not load on WM. Children have a free choice whether to play the game. After each week of training the child receives a small reward (e.g. doing something fun with dad, choosing dinner).

In the original version children train for a period of 5 weeks (25 days and 200 exercises in total), with an estimated time spent per day between 35 and 50 min. The less intensive but prolonged version has a duration of 8 weeks (30 days and 160 exercises in total), with an estimated time spent per day between 25 and 35 min. In both versions a licensed Cogmed coach will provide detailed personalized coaching and feedback on the child’s performance following a strict protocol, by telephone in 5 sessions with the parent, or aide and also with the participating child. In the original version this means a coaching contact ones a week. To keep additional mental health care costs similar with the original Cogmed version (consisting of five weeks of training and weekly feedback). This means a coaching contact every one and a half week in the prolonged version.

*Cogmed WMT has been developed by Cogmed Cognitive Medical Systems AB (Stockholm, Sweden). Pearson is the official publisher for the Netherlands for Cogmed. BeterBrein provides the educational program to become a licensed Cogmed coach.*

### Interventions

#### Condition 1: A less intensive and prolonged version of Cogmed WM training with active coaching and personalized feedback

This coaching condition aiming to increase performance and motivation is suggested by Cogmed to be the best way to deliver the intervention. During 8 weeks each child will train for an average of 30 min (5 exercises) a day, 4 days a week. The training program consists of WM tasks implemented on a computer program. Three persons are directly involved in the treatment program: (1) The child undergoing the training, (2) parents, teachers or mentors (aides) whose role is to motivate the child during the training, who will have contact with the coach and act as an intermediary between the coach and the child, (3) the licensed Cogmed coach trained by BeterBrein, who will provide detailed personalized coaching and feedback on the child’s performance by telephone in 5 sessions with the parent, and aide (if involved) and the child. Detailed personalized coaching and feedback means explaining in what way the performance can be optimized, by analyzing how and when mistakes are made (the Cogmed coach can log in on the child’s account). For example; performances are better when a child is training in the morning, or a child will perform better when he/she starts with the more difficult exercise(s), or when he/she takes more short breaks. The coach gives this feedback to the child, parent(s) and aid(es). Secondly, motivational aspects are an important part of detailed personalized coaching and feedback. The coach explains why the training is helpful for a better daily functioning and asks the persons involved if everybody sticks to the rewarding plan and if changes have to be made. Furthermore, suggestions in how to motivate the child will be discussed when motivational problems occur. The suggestions are personalized and tailor-made for their specific home situation. The coach, a psychologist or psychological assistant at Karakter, will follow a strict protocol, as part of the training program. According to the protocol the coach will start with a standardized training instruction, in which a demonstration of the training will be given and specific goals (e.g. improvement of memory- or attention span, or better results at school) will be determined. Training days and training times will be discussed and agreements about who will act as aid will be made. Furthermore a rewarding system will be agreed on. During the coaching calls the Cogmed coach will discuss standardized topics such as training progress (e.g. time schedule, training results) by logging in to the Cogmed server to review the child’s exact performance for each training day, to optimize training performance. Also motivation is a standard topic to discuss (e.g. rewarding system, goals).

#### Condition 2: A less intensive and prolonged version of Cogmed WM training without active coaching and personalized feedback, only general non-personalized coaching

This version is exactly the same as the training in the active condition, except for the personalized coaching and feedback. The general non-personalized coaching condition will also start with a standardized training instruction with the same topics, accept for the determination of the specific goals and the use of a rewarding system. The coach will spend the same amount of time with the parents or aid(es) at school and/or child on the telephone, but will not log in on the Cogmed server to see the child’s exact performance. Only concrete training logistics (e.g. training time, training minutes, breaks during the training etc.) will be assessed.

### Measures and procedures

The selection phase will be started once written informed consent has been obtained. Parents will be asked demographic and background information such as previous care and medication use. Parents will also be asked to complete the Diagnostic Interview Schedule for Children (DISC-IV), a highly structured diagnostic instrument designed for use by non-clinicians [15] to assess the presence of ADHD and the exclusion of other comorbid psychiatric disorders. The Social Communication Questionnaire (SCQ) will be used to assess the presence of ASD [16]. These results will be checked against the DSM-IV criteria by an experienced psychologist. Where the most recent results are >2 years old intellectual disabilities will then also be checked before participation through 5 subtests of the WISC-III-NL (Information, Vocabulary, Picture Completion, Block Design, Digit Span) [17]. Children who meet the inclusion criteria will be included in the study. The assessment of neurocognitive functioning domains (WM and executive functioning), academic achievements (arithmetic and reading), behavioral problems and parenting style will be administered at 3 consecutive points: at baseline, directly after treatment and 6 months after treatment. The child will undergo a test battery that will measure neurocognitive functioning, consisting of tests capturing visual [18, 19] and verbal WM [19], sustained attention [20], response inhibition [20] and goal-directed behavior [21]. Academic performance will be measured with a speed reading test [22] and a speed math test [23]. Parents will complete a Dutch translation of the Alabama Parenting Questionnaire (APQ), to measure parenting style [24]. Parents and teachers will complete the Vragenlijst voor Inventarisatie van Sociaal gedrag van Kinderen (VISK, Social Behavior Inventory) [25], the ADHD Vragenlijst (AVL, ADHD Questionnaire) [26] and the Behavior Rating Inventory of Executive Function checklist (BRIEF) [27]. Five (telephone) coaching contacts will take place during the training phase. After completing the training children and parents/teachers in both groups will be questioned about their motivation (e.g. how much fun was it to do) and satisfaction of treatment a scale from 0 to 10. All tests and questionnaires have been selected based on clinical experience with the population and are in line with the international literature. Other aspects taken into account will be the duration of administration, the combination of neurocognitive tests required to determine proximal/near (visual and verbal WM) and distal/far (sustained attention, response inhibition and goal-directed behavior) transfer effects and methodological issues such as presence of Dutch norms and test-retest reliability. See Table 1 for an overview of the assessments and outcome measures.

**Table 1 Tab1:** Measurements

	Measure	Informant	T0	T1	T2	T3
*Selection fase*	*Shortened version of the Wechsler Intelligence Scale for Children-III-NL:* subtest Information, Vocabulary, Picture Completion, Block Design, Digit Span, which gives an estimation of the Total IQ**	child	*			
	Diagnostic Interview Schedule for Children (DISC-IV): structured diagnostic interview, registered via the internet, Measures presence of symptoms and criteria variables as defined by the DSM-IV. Only domains ADHD (inclusion criterion) and major depression, bipolar disorder, psychotic disorder, conduct disorder and general anxiety disorder (exclusion criteria) are administered.	parent	*			
	Social Communication Questionnaire (SCQ): a quick screening questionnaire of 40 items for autism spectrum disorders.	parent	*			
*Primary outcome*	*Backward block recall:* subtest from the Working Memory Test battery for Children, measures visual working memory.	child		*	*	*
*Secondary outcome*	*Spatial span: subtest from* Automated Working Memory Assessment, measures visual working memory	child		*	*	*
	*Backward digit recall:* subtest from the Working Memory Test battery for Children, measures verbal working memory.	child		*	*	*
	*Listening recall:* subtest from the Working Memory Test Battery for Children, measures verbal working memory.	child		*	*	*
	*Sustained Attention Dots:* subtest from the Amsterdam Neuropsychology Test battery, measures sustained attention.	child		*	*	*
	*Go-Nogo:* subtest from the Amsterdam Neuropsychology Test battery, measures the ability to inhibit automatic responses.	child		*	*	*
	*Comprehension of instruction:* subtest from Nepsy-II-nl, measures the ability to receive, process and execute oral instruction of increasing syntactic complexity.	child		*	*	*
	*Speed math (Tempo Test Rekenen):* measures degree of automation of addition, subtraction, multiplication and decision.	child		*	*	*
	*Speed reading (Een minuut test):* measures technical literacy speed.	child		*	*	*
	*Vragenlijst voor Inventarisatie van Sociaal gedrag van Kinderen (VISK):* measures symptoms of ASD on a 4-point Likert scale.	parent/ teacher		*	*	*
	*ADHD Vragenlijst (AVL):* assess symptoms of ADHD on a 4-point Likert scale	parent/ teacher		*	*	*
	*Behavior Rating Inventory of Executive Function checklist (BRIEF):* 70 item questionnaire designed to assess executive functioning on a 3-point Likert scale in home and school environments.	parent/ teacher		*	*	*
	*Alabama Parenting Questionnaire (APQ):* assess parenting style and indirectly coaching style on a 5-point Likert scale.	parent		*	*	*

*T0 = selection fase, T1 = baseline, T2 = directly after treatment, T3 = follow-up (6 months)*

^**^Intelligence Quotient is only administered if IQ data are not available or when IQ test had been administered more than 2 years ago

Participants can leave the study at any time for any reason if they wish to do so without any consequences. The principal investigator can also withdraw a subject if: The investigator believes that for safety reasons (e.g. in the presence of adverse events) it is in the best interest of the subject to stop treatment, the subject is unwilling to cooperate for reasons not related to the trial treatment, an intercurrent illness emerges of which the severity, duration, or required treatment violated the conditions of the trial. Reasons for withdrawal are recorded. Participants withdrawn from the study for a medical reason will be followed until the adverse events have been resolved.

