### Aims

The overall purpose of the study is to gain insight into Cogmed WMT, and in particular to identify which elements may help to develop individually tailored effective treatment possibilities for groups of vulnerable children.

The primary aim of this study is to investigate the efficacy of a less intensive but prolonged Cogmed RM WMT with active personalized coaching and feedback in children with MBID and neuropsychiatric disorders, compared to a less intensive but prolonged RM Cogmed WMT without personalized (i.e. only general non-personalized) coaching and feedback, on neurocognitive functioning as measured with the backward block recall task.Secondly, the efficacy of active personalized coaching will be investigated on various other neurocognitive functioning domains (WM and executive functioning), academic achievements (arithmetic and reading), behavioral problems and parenting style.

It is hypothesized that participants who receive a less intensive but prolonged RM Cogmed WMT with active personalized coaching and feedback demonstrate greater improvement on neurocognitive functioning, academic achievements, behavioral problems and parenting style, directly after training and 6-months post baseline, compared to those who receive a less intensive but prolonged RM Cogmed WMT with only general non-personalized coaching and feedback.

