### Design

Two groups of 26 children will train 8 weeks, 4 days a week for an average of 30 min (5 exercises) each day in a double-blind randomized controlled trial. Parents, children and teachers will be blinded for the group allocation, i.e. 1. personalized coaching and feedback or 2. non-personalized feedback and general coaching. All participants will undergo a behavioral and neurocognitive assessment including academic achievement measures (pre- and post- assessment). The post-assessment will be carried out in the week after the last session, and an evaluation of the training will take place. In this evaluation parents are questioned about their positive and negative experiences with the training. Furthermore they are asked if they would recommend the training to others and to grade their contentment with the training between 0 (very poor) and 10 (very good). Six months after the last training session there will be a follow-up. Selection of participants, screening for eligibility and assessments will be performed at Karakter, Centre for child and adolescent psychiatry. The training will be done at home and/or at school.One group will be treated with a less intensive but more prolonged version of the Cogmed WMT, version R/M. They will receive personalized coaching and feedback (5 sessions) based on their actual performance during the training;One group will be treated with a less intensive but more prolonged version of the Cogmed WMT, version R/M. They will receive the same amount of coaching time, but without personalized feedback (only non-personalized coaching).

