## Discussion

It is of great importance to undertake a treatment-efficacy study in this large vulnerable population of children with MBID and co-occurring psychiatric disorders. Evidence-based treatment possibilities are scarce for these children, since they are often excluded from participation in scientific research due to the heterogeneity of the population. If a less intensive but more prolonged version of the Cogmed WMT intervention with active coaching and feedback appears to improve neurocognitive functioning, academic achievements and/or behavioral problems, it can be implemented in mental health care and special education schools as an evidence-based intervention for children with MBID and neuropsychiatric disorders. Our study also adds to the literature in that this will be the first study to compare effects of different types of coaching. This aspect is of great value, since several studies have shown significant improvements on both the WM condition as well as the placebo condition if coaching is not personalized. Furthermore, a less intensive and more prolonged WMT would probably better fit these children and might result in an increased training benefit and less dropout. On the other hand one could argue that 4 training sessions a week, for a period of 8 weeks, with a shorter duration of training time a day, is indeed less intensive than 5 training sessions a week, for a period of 5 weeks, with a longer duration of training time a day.

Finally, one strength of this study is the double-blind randomized controlled design, which is the most robust design in trials attempting to establish efficacy. This design not only takes into account near transfer effects, but also far transfer effects. These effects are measured up to 6 months after training.

In this study, the second (non-personalized) coaching condition might be a challenge in clinical practice. Coaches should not be tempted to give any substantive feedback to the parent on how to motivate their child when training difficulties occur. On the other hand, a greater degree of training dropout might take place when non-personalized coaching is performed more rigidly. One limitation of this study is the use of single tasks to assess the generalization effects of WMT. It remains unclear whether any improved performance will be due to an acquired underlying ability and/or reflect practice effects. Therefore the results may have to be interpreted cautiously.

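### The hypothesis dates the last follow-up about 8 weeks earlier than the design does; separately, a safety stop of training can become withdrawal from the study, which may cost a few T2/T3 scores

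*Protocol article*

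**What the plan says.** **Date of T3.** The hypothesis in Aims places the expected benefit "directly after training and 6-months post baseline". Design says: "Six months after the last training session there will be a follow-up". Measures and procedures lists the assessments "at baseline, directly after treatment and 6 months after treatment". Discussion, naming the design's strengths, says: "These effects are measured up to 6 months after training". The note under Table 1 reads "T3 = follow-up (6 months" and names no starting point; the abstract gives none either.

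**Withdrawal.** The text after Table 1 begins a list of grounds with "The principal investigator can also withdraw a subject if". The first ground is the investigator's belief that "for safety reasons (e.g. in the presence of adverse events) it is in the best interest of the subject to stop treatment". The other two are unwillingness to cooperate for reasons unrelated to the treatment, and an intercurrent illness that breaches the trial's conditions. The paragraph ends: "Participants withdrawn from the study for a medical reason will be followed until the adverse events have been resolved".

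**Analysis.** Statistical analysis specifies an ANOVA of backward block recall with group and three time points, and takes the group-by-time interaction as the treatment effect. It promises intention-to-treat analyses in case of withdrawal, discontinuation or missing data, and refers there to children who missed more than five sessions.

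**The concern.** The hypothesis is the sentence against which the results will be read. If its date is taken at face value, T3 falls roughly four months after training and does not test the six-month durability that Discussion presents as a strength. T3 is also a level of the time factor in the primary test, so its date is part of what that test means.

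The withdrawal rule raises a different issue. The ground concerns stopping the training, but the consequence is leaving the study. A safety reason to stop a computer training does not in itself prevent a block-recall test or a parent questionnaire. The ANOVA as described uses a child only if all three scores exist or a missing one is filled in, and a measured score is better than a filled-in one. An analysis plan can choose how to handle a missing score, but it cannot collect one from a child who has already been withdrawn.

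**Working it through.** **1. Date of T3**

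Inputs: training lasts 8 weeks (Design). Assumptions: training starts directly after baseline, since the gap is not stated, and 6 months = 26 weeks.

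| Source | Counted from | Weeks from baseline | Weeks after last session |
|---|---|---|---|
| Aims | baseline | 26 | 26 − 8 = 18 |
| Design | last training session | 8 + 26 = 34 | 26 |
| Measures and procedures | end of treatment | 34 | 26 |
| Discussion | end of training | 34 | 26 |
| Table 1 note | not stated | – | – |

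- Gap between the two dates: 34 − 26 = 8 weeks.
- Under Aims, T3 comes 18 weeks after training, or 18 / 4.35 = 4.1 months.
- The interval after training is shorter by 1 − 18/26 = 31%.

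**2. Scale of the withdrawal point**

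Inputs from Sample size: 52 children enrolled, 50 planned for analysis, 4 of 76 lost in the earlier study, power 79% at an effect size of .40 and 93% at .50 with baseline as covariate. Alpha is 5% (Statistical analysis).

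The plan's own figure first. Assume that its effect size is Cohen's f and use the F test for two groups with one covariate: df = (1, N − 3), noncentrality = N × f².

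- N = 50, f = .40: noncentrality 50 × 0.16 = 8.0, power 79.1% (plan: 79%).
- N = 50, f = .50: noncentrality 50 × 0.25 = 12.5, power 93.4% (plan: 93%).

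Both figures reproduce. Expected losses at the plan's rate are 52 × 4/76 = 2.7, so about 3. That is all losses together. Families may also leave by their own choice, and no reasons are given for the four earlier dropouts, so the number that a retention rule could recover lies between 0 and about 3.

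| Children analysed | Noncentrality at f = .40 | Power |
|---|---|---|
| 52 | 52 × 0.16 = 8.32 | 80.7% |
| 50 (plan) | 8.00 | 79.1% |
| 49 (52 − 3) | 49 × 0.16 = 7.84 | 78.3% |

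- Cost of three losses against the plan: 79.1 − 78.3 = 0.8 point.
- Most that could be regained: 80.72 − 78.26 = about 2.5 points, and only if every lost child were recovered.

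This is the plan's between-group power, not power for the group-by-time test, so it shows scale only.

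**The case against.** On the date, the two sections that set the schedule agree with each other, and Discussion agrees with them. Staff running the trial would follow Design. A reader might infer that the visit is undecided by 8 weeks for all 52 children. The documents do not support that: one phrase in the hypothesis is out of line, and it is probably a slip. What stands is that the slip sits in the hypothesis, and that the Table 1 note does not correct it.

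On withdrawal, the rule is permissive. It says that the investigator can withdraw a child, and it nowhere cancels T2 or T3. Following medical cases until adverse events resolve may be a safety minimum, not a limit on other data. Statistical analysis names withdrawal and discontinuation separately and expects some incompletely trained children to be analysed. An article may also leave the detail of continued assessment to the full protocol. A reader might infer that every child who stops training is lost to assessment, or that the result is biased. Neither follows from the text. What stands is narrower: the paragraph as published moves from stopping treatment to leaving the study without separating them, and the only later contact it states is for adverse events. Unwillingness and illness are covered only where testing is still possible, since both can include refusing or being unfit for tests.

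A reader might also conclude that all visits should be timed from the planned end of training. That goes too far. For a child who finishes in, say, week 10 (an assumption), a visit at week 34 would fall 24 weeks after the last session and so shorten the interval that matters.

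**Conclusion.** The date is wrong as written in Aims: about 8 weeks earlier than in the three other places, or 18 weeks instead of 26 after training. This assumes that training follows baseline directly. It concerns a stated time point of the primary analysis and is the firmer of the two points.

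The withdrawal wording is a cheap improvement with a small effect. Between 0 and about 3 children are at stake. Three losses cost 0.8 point of power against the plan, and at most about 2.5 points could be regained, reading the plan's effect size as Cohen's f. The direction of any bias is unknown and none is claimed. The change is still worth making, because the promised intention-to-treat analysis needs scores that only a retention rule can secure.

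**What to change.** 1. **Aims:** replace the post-baseline date with six months counted from the last session of training, and put the same starting point in the Table 1 note. Design and Measures and procedures stay as they are.
2. **Text after Table 1:** add that a child whose training is stopped stays in the study and is invited to T2 and T3 at the dates planned for a completer (about weeks 9 and 34 from baseline), unless assessment is refused, consent is withdrawn or testing is medically unsafe. The grounds for stopping training do not change. Children who complete training, including those who finish late, keep the last-session anchor.

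Cost: a small wording amendment that reuses visits already planned, with no extra children. The downside is that some families will decline the visits, and scores obtained after training has stopped may slightly dilute the contrast between the groups.
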